## Abstract

**Background:**

Post-viral syndromes, including long- and post-COVID, often lead to persistent symptoms such as fatigue and dyspnoea, affecting patients' daily lives and ability to work. The COVI-Care M-V trial examines whether interprofessional, patient-centred teleconsultations, initiated by general practitioners in cooperation with specialists, can help reduce symptom burden and improve care for patients.

**Methods:**

To evaluate the effectiveness of the intervention under routine care conditions, a cluster-randomised controlled trial is being conducted. The primary outcome is physical performance, assessed by the difference between the actual and individually defined target distance in the 6-min walk test. Secondary outcomes include health-related quality of life (PAC-19QoL), cognitive function (DemTect), lung function (peak flow meter), fatigue symptoms (FAS), and weekly working hours, measured at baseline (T0) and after four months (T1).

**Results:**

In the absence of evidence-based therapies for post-viral symptom complexes, multidisciplinary care and support currently represent the mainstay of patient management. The COVI-Care M-V study evaluates a regionally tailored, patient-centred intervention, developed based on qualitative research and piloting. Anticipated challenges include selection bias, recruitment difficulties due to healthcare staff shortages, and underreporting of symptoms, which will be addressed through targeted awareness materials and digital support for participating practices.

**Conclusions:**

This study aims to generate evidence to enhance care, particularly by optimising healthcare structures for affected individuals.

**Trial registration:**

ISRCTN, ISRCTN11050086. Registered 28 April 2025

**Supplementary Information:**

The online version contains supplementary material available at 10.1186/s12913-025-13276-6.

## Contributions to the literature

• Illnesses after a viral infection, like post-COVID, can cause many symptoms, such as tiredness or trouble breathing. Because these symptoms vary so much, it is often difficult for doctors to diagnose the condition.• Apart from individual therapeutic approaches that alleviate individual symptoms, there are currently no medications available to treat the disease.• Currently, the best way to support patients is through care from different types of healthcare professionals working together.• This study looks at whether video consultations, where general practitioners and specialists team up to help patients, can reduce symptoms and improve quality of life.

## Background

Post-viral syndrome including long- and post-COVID refers to a range of health conditions that patients suffer from after surviving various viral infections, including flu, a SARS-Cov-2 primary infection, and others [1]. Although the exact prevalence of long- and post-COVID cannot yet be clearly determined for Germany due to a lack of population-representative studies, studies point in the same direction. According to the German study by Peter et al. (2022), the estimated prevalence of post-COVID is at least 6.5%, 6 to 12 months after a SARS-Cov-2 infection [2]. Unfortunately, more recent representative data do not exist. The most common long-term symptoms include persistent fatigue and dyspnoea, as well as cardiovascular and neurological complaints. Four symptom complexes from the pulmonary, cardiological, angiological, and psychological areas are often distinguished [3]. Symptoms may persist, recur, or fluctuate after initial recovery from acute SARS-CoV-2 infection [4]. Long- and post-COVID is thus a complex condition with long-lasting, heterogeneous symptoms [5]. Especially for people in employment, the condition can pose a major challenge, making a (full) return to work considerably more difficult. The same applies to patients with other post-viral conditions, especially myalgic encephalomyelitis/chronic fatigue syndrome (ME/CFS). ME/CFS patients not only experience significant physical weakness (fatigue) that severely limits their activities, but also neurocognitive and immunological symptoms. Before the COVID-19 pandemic, the number of patients in Germany was estimated at around 250,000 [6]. ME/CFS often occurs after an infectious disease, with various pathogens such as Epstein-Barr virus and influenza known to trigger it. During the COVID-19 pandemic, it became apparent that a subset of patients with long- and post-COVID also develop ME/CFS [7].

In Germany, the interdisciplinary S1 guideline Post-COVID/Long-COVID from the Association of the Scientific Medical Societies in Germany (Arbeitsgemeinschaft der Wissenschaftlichen Medizinischen Fachgesellschaften, AWMF) offers initial guidance on diagnostic and therapeutic options [8]. Furthermore, comprehensive treatment of those affected requires interprofessional structures and networks, which so far only exist to a limited extent in Germany. This applies particularly to rural and structurally weak regions. Patients experience bottlenecks in diagnosis, further treatment and outpatient follow-up care after rehabilitation stays. The Long-COVID Initiative of the German Federal Ministry of Health is currently funding a series of research projects aimed at optimising the care of those affected. The COVI-Care M-V study presented here is also being financed by these funds.

## Methods

### Aim

The COVI-Care M-V cluster-randomised controlled trial investigates the extent to which interprofessional, patient-centred teleconsultation, initiated and supervised by the general practitioner (GP), helps to reduce symptoms of patients with long- and post-COVID and other post-viral symptom complexes. The intervention focuses on the interprofessional exchange between the GP and the patient with specialists for long- and post-COVID at the Rostock University Medical Center.

### Trial design

To examine the effectiveness of the intervention in routine care, we are conducting a cluster-randomised controlled intervention study. Primary outcome is physical performance, measured as the difference between the actual value and an individually defined target value for the walking distance in the 6-min walk test [9]. Secondary endpoints include health-related quality of life (PAC-19QoL) [10], cognitive impairment (DemTect) [11], lung function (peak flow meter) [12], fatigue symptoms (FAS) [13], and weekly working hours. These will be measured before the intervention (T0) and four months later (T1). The trial description is structured in accordance with the CONSORT Statement [14].

### Setting

Mecklenburg-Western Pomerania is a predominantly rural and partly economically weak region with small and medium-sized towns. There are hardly any metropolitan urban centres. In a Germany-wide comparison, demographic aging is particularly advanced here and has been leading to an increase in older patients with chronic diseases and multimorbidity for years. This is accompanied by a decline in the number of healthcare professionals, which is currently reflected in a reduction in health care services. Specialist medical care close to home is not equally accessible to all patients [15]. In particular, specialised outpatient clinics for post-viral symptom complexes are very limited. However, even in large cities, it is not always possible for those affected to see specialists due to their fatigue symptoms.

### Recruitment

The recruitment of physicians will be carried out by writing to GPs in private practice in Mecklenburg-Western Pomerania. For this purpose, a complete list of the Association of Statutory Health Insurance Physicians in Mecklenburg-Western Pomerania will be used. Enough GPs will be contacted in waves until the required number is reached. In addition, existing networks such as the teaching and research networks of the Institute of General Practice at Rostock University Medical Center will be used. Patients will be selected consecutively in the participating practices based on the inclusion and exclusion criteria below. Posters will also be used in GP practices to support patient recruitment and to motivate patients to proactively approach their GP about the study. Studies suggest that some of those affected do not address existing symptoms with their GP for a variety of reasons [16]. After being informed by the participating GPs and signing the declaration of consent, patients are included in the study.

### Inclusion and exclusion criteria

The study will include at least 42 GPs and their patients suffering from post-viral symptom complexes. Patient-related inclusion criteria are the presence of a post-viral symptom complex and an age of at least 18 years.

We will include patients with sequelae of viral infections, with consideration given to the following ICD codes:U09.9! Post-COVID-19 condition, unspecifiedU10.- Multisystem inflammatory syndrome associated with COVID-19J10.- Influenza due to identified influenza virusJ11.- Influenza, virus not identifiedU07.1! COVID-19, virus detectedU07.2! COVID-19, virus not detectedB27.- Infectious mononucleosisG93.3 Chronic fatigue syndrome [CFS], including post-viral (chronic) fatigue syndromeJ06.9 Acute upper respiratory infection, unspecified

Furthermore, to be included, patients must exhibit at least three symptoms from different symptom complexes:Neurological/Neuromuscular/Psychiatric:G93.3 Chronic fatigue syndromeF06.7 Cognitive impairmentU51.- Cognitive dysfunctionF51.9 Nonorganic sleep disorder, unspecifiedM79.1 MyalgiaM25.5 Joint painM62.81 Muscle weakness (generalised)R51 HeadacheU50.- Motor dysfunctionF43.- Reaction to severe stress and adjustment disordersR26.- Gait and mobility disordersF41.9 Anxiety disorder, unspecifiedF32.- Depressive episodeF43.- Reaction to severe stress and adjustment disordersCardiovascular:I47.9 Paroxysmal tachycardia, unspecifiedI95.1 Orthostatic hypotensionR00.2 PalpitationsR42 DizzinessPulmonary:R06.0 DyspnoeaU69.6 Chronic coughR07.1 Chest pain during breathingOther:R43.- Disorders of smell and tasteR10.4 Other and unspecified abdominal painL65.- Hair lossK59.- Other functional bowel disordersT78.1 Other food intolerance, not classified elsewhere

Patient-related exclusion criteria are the presence of an acute malignant underlying disease, a remaining life expectancy of less than 12 months as estimated by the GP, language barriers (e.g. hearing impairment, insufficient language skills) or dementia and the lack of capacity to consent.

### Intervention

The intervention focuses on the interprofessional exchange between the GP and patient with a specialist from the Long-COVID-Board at the Rostock University Medical Center using teleconsultation. The interdisciplinary Long-COVID-Board regularly discusses individual patient cases, quality of outcomes, and established diagnostic and treatment procedures, to develop and share best practice models. On the one hand, this approach enables patients to receive care close to home, in familiar structures. On the other hand, a specialist re-evaluates the diagnosis and therapy of the included patients based on specific experience and expertise in the treatment of post-viral symptom complexes. Various symptoms in the pulmonary, cardiological, angiological and neurological areas can thus be considered holistically and further procedures in diagnostics and therapy can be discussed. Each appointment is planned to last 45–60 min and is prepared by the GP in advance by sending the patient report. At the same time, patients are actively involved in the decision-making process. During the teleconsultation, they are on-site in the GP's practice together with their GP on the screen and personally report their complaints and symptoms. They are actively involved in the subsequent consideration of further diagnostic and therapeutic steps. Before the intervention begins, all GPs in the intervention group receive two online training sessions. A 120-min training session addresses current therapeutic approaches in the treatment of post-viral symptom complexes and is conducted by specialists from the Long-COVID-Board. A second training session, which lasts about 90 min, is dedicated to the communicative aspects of conducting teleconsultations and the associated effects on the doctor-patient relationship. Also, techniques of patient-centred communication are taught here. The participating doctors receive an expense allowance per patient. See Tables 1–3 in the supplement for detailed information.

### Technical solutions

This study integrates standardised data collection and technically robust as well as secure teleconsultation service for patients with post-viral symptom complexes in primary care. Both study groups utilise uniform technical setups, centred on the MEYCARE® Set, which includes a tablet personal computer, Bluetooth-enabled medical devices, and an internet connection via a multi-SIM (Subscriber Identity Module) LTE (Long-Term Evolution) network, ensuring optimal connectivity even in rural practices. Data collection is streamlined through the digital trial platform (PDE—Process Development Execution), enabling consistent instrumental measurements and patient self-reports via a digitised questionnaire. All data are securely processed and stored in MEYCLOUD, certified under DIN EN ISO/IEC 27001, using highly regulated access via a VPN (Virtual Private Network) tunnel and encrypted data sharing. MEYTEC provides operational support, including replacement devices to minimise downtime. Teleconsultations use the MEYDOC® solution for end-to-end encrypted audiovisual communication, with tailored training provided to participating practices.

### Randomisation and control group

All participating practices will be randomly assigned to the intervention or control group in a 1:1 ratio centrally by the Institute for Medical Biometry and Epidemiology at the University Medical Center Hamburg-Eppendorf. Block-randomisation with variable block length will be used. Patients’ baseline (T0) characteristics can only be collected after randomisation of GPs but before start of intervention.

The participating patients of a practice are thus either completely in one group or the other (cluster-randomisation). Contamination effects are thus avoided. Patients in the control group receive conventional care (care as usual) and an information brochure about post-viral symptom complexes. After data collection, general practitioners in the control group will have the opportunity to participate in both online training courses on post-viral symptom complexes and communicative aspects of teleconsultations. This is to prevent practices from dropping out of the study prematurely. Physicians in the control group will also receive compensation for each included patient.

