### Blinding

This study does not involve the blinding of patients and study staff. Data analysts will be blinded partially.

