The COVI-Care M-V study benefits from an intervention that was specifically developed based on findings from a qualitative interview study, ensuring its alignment with regional healthcare structures. Additionally, the study design was pretested in a small pilot study to assess and optimise the feasibility of recruitment and data collection in the primary care setting. The randomised controlled design, which accounts for a 30% dropout rate in its calculations, aims to generate reliable results. Study endpoints are comprehensively defined, incorporating both physical and mental health aspects. A strong emphasis on the patient-centred outcome of health-related quality of life further enhances the study’s design and its overall validity. To achieve the required sample size, an extended recruitment period of two years is planned. Moreover, participating practices benefit from optimised digital data collection and continuous support from the study team.

Despite its strengths, the study is subject to certain limitations. Participation will likely be skewed toward practices with a higher affinity for technology, while those less inclined toward healthcare innovation may be underrepresented. Due to the complexity of the intervention and its requirements, neither the GPs nor the patients can be blinded. The allocation of patients cannot be concealed. Additionally, the healthcare landscape in Mecklenburg-Western Pomerania presents challenges for study participation, including physician shortages, limited practice staff, and an increasing patient burden due to demographic shifts. Preliminary studies indicate that some affected individuals do not always disclose post-COVID symptoms to their GP for various reasons. To address this, educational brochures and practice posters will be utilised to raise awareness. Furthermore, some patients included in the study may already be receiving specialist care.

This study aims to generate evidence to enhance care, particularly by optimising healthcare structures for affected individuals.

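### Patients appear to be recruited after their unblinded practice knows its arm, and neither the stated remedies nor the primary model, which adjusts only for baseline walking, deals with different recruitment by arm

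*Protocol article*

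**What the plan says.** **Allocation.** Under Randomisation and control group, the article states: "All participating practices will be randomly assigned to the intervention or control group in a 1:1 ratio centrally". The same section says that patients' baseline (T0) characteristics "can only be collected after randomisation of GPs but before start of intervention".

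**Recruitment.** The Recruitment section says: "Patients will be selected consecutively in the participating practices based on the inclusion and exclusion criteria below". Posters in practices are meant "to motivate patients to proactively approach their GP about the study". Enrolment then follows: "After being informed by the participating GPs and signing the declaration of consent, patients are included in the study".

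**Blinding and concealment.** Blinding states: "This study does not involve the blinding of patients and study staff". The Discussion adds that GPs cannot be blinded either, and concedes: "The allocation of patients cannot be concealed".

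**Training.** The Intervention section says: "Before the intervention begins, all GPs in the intervention group receive two online training sessions". One session is 120 minutes on treating post-viral symptom complexes; the other is about 90 minutes on communication. Control GPs are offered both courses only after data collection.

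**Analysis.** The primary mixed model in Statistical methods has the baseline walking difference and group as fixed effects, and practice as a random effect. A further mixed model of the primary endpoint adds clinically important baseline covariates. The example given is covariates that show clinically relevant group differences.

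**Remedies.** The Abstract names selection bias as an anticipated challenge. The measures it lists for its anticipated challenges are awareness materials and digital support for practices. The Discussion's limitations cover which practices take part, workload and under-reporting of symptoms.

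**The concern.** Randomising practices makes the practices comparable. The patients are comparable only if their enrolment does not depend on the arm. Here the arms offer patients and GPs different things. Intervention patients are offered a specialist teleconsultation of 45 to 60 minutes, in a region where the Setting section describes specialised clinics as very limited. Control patients are offered usual care and a brochure. Intervention GPs must prepare a report and attend each consultation; control GPs need not. Who is approached and who agrees could therefore differ by arm.

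If so, the estimated effect would mix the effect of teleconsultation with differences in who was enrolled. Adjusting for baseline walking removes the part carried by that measurement. It does not remove differences in fatigue, comorbidity, illness duration or motivation that predict the four-month result at a given baseline. A larger sample would not help, because it narrows the interval around a biased estimate.

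**Working it through.** **1. Order of events.** The sections are read together:
- Randomisation and control group: practices are allocated, and T0 measurement comes afterwards.
- Recruitment: the practice selects, the GP informs, the patient consents.
- Blinding and Discussion: patients, GPs and study staff are unblinded, and patients' allocation is not concealed.
- Nothing in the article describes enrolment before allocation, or a recruiter blind to arm.

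That identification and consent follow disclosure of the arm is therefore an inference, but the natural one. The timing statement itself covers T0 data only.

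**2. Order of training.** Training and T0 are both placed before the intervention. Their order relative to each other, and to recruitment, is not stated.

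**3. Reproducing the plan's sample size.** Inputs from Sample Size: difference 10 points (83% against 93%), SD 19, 4 evaluable patients per practice, ICC 0.15, two-sided 5%, power 80%.
- Per arm without clustering: 2 × (19 × (1.960 + 0.842) / 10)² = 56.7.
- Design effect: 1 + (4 − 1) × 0.15 = 1.45.
- Per arm with clustering: 56.7 × 1.45 = 82.2, which needs 21 practices of 4, or 84 patients.
- Total: 168 evaluable; 168 / 0.70 = 240 recruited.

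The stated figures reproduce and are not in dispute.

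**4. Planned standard error of the group difference.** 19 × √(2 × 1.45 / 84) = 3.53 points.

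**5. What an assumed residual bias would do.** With no true effect and a bias b remaining after baseline adjustment, type I error = P(Z > 1.96 − b/3.53) + P(Z < −1.96 − b/3.53).

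| Assumed b | In SD units | b / 3.53 | Two-sided type I error |
|---|---|---|---|
| 0 | 0 | 0 | 5.0% |
| 1.9 points | 0.1 | 0.54 | 8.4% |
| 3.8 points | 0.2 | 1.08 | 19.0% |

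A bias of 3.8 points is 38% of the planned 10-point effect.

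**6. How such a bias could arise (assumption).** Suppose a prognostic factor is imbalanced by d SD and has correlation r with the outcome given baseline walking. The bias is then about r × d × 19. With r and d each between 0.2 and 0.5, it runs from 0.2 × 0.2 × 19 = 0.76 points (type I error 5.5%) to 0.5 × 0.5 × 19 = 4.75 points (27%).

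**7. The opposite direction.** If the bias worked against the intervention, power would fall. Planned power by the normal approximation is 80.9%. A bias of −1.9 points gives (10 − 1.9) / 3.53 = 2.29, and P(Z > 1.96 − 2.29) is about 63%. A bias of −3.8 points gives (10 − 3.8) / 3.53 = 1.76, and about 42%.

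**The case against.** **Consecutive selection on common coded criteria.** This is a real safeguard, and the same criteria apply in both arms. It stands as partial protection. Unblinded practices apply it, however, and it does not govern who consents. That the article shows no screening log is not a fault, since the full protocol may contain one.

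**A covariate-adjusted model is already planned.** It is, so a reader should not infer that adjustment stops at baseline walking. But that model is not the primary analysis. Its covariates are exemplified by observed imbalance, so they may depend on the data. It also cannot correct for unmeasured differences.

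**Training.** A reader might infer that intervention GPs are trained before they recruit and so recognise different patients. The documents do not support this as fact: training is dated only relative to the intervention, and its content is treatment and communication, with no mention of case-finding. It adds to the risk only if it precedes recruitment. The concern about unconcealed allocation does not depend on it.

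**Posters.** They are described for practices generally. Self-referral alone creates no difference between arms.

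**Size.** A reader might take the 8% and 19% as the trial's actual error rates. They are not. The bias sizes are assumed, and the standard error uses the planned SD of 19 without any gain from baseline adjustment.

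**Disclosure.** The article concedes the lack of blinding and concealment and names selection bias in general terms. This is also a familiar weakness of cluster trials that recruit after randomisation. Both points are fair, but different patient recruitment by arm is never named, and the listed measures do not address it.

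**Conclusion.** The concern holds as a documented risk to the primary comparison. Read together, the sections put recruitment in the hands of unblinded practices that most naturally already know their arm. The stated remedies address under-reporting and workload, and the primary model adjusts for one baseline measure only. The article contains no wrong figure on this point, and it does not show that the arms will differ.

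The size is unknown. An assumed residual bias of 0.1 to 0.2 SD would move the type I error from 5% to between about 8% and 19% in one direction, or cost power in the other. The conclusion rests on the inference that consent follows disclosure of the arm. If the full protocol has patients identified and consented before disclosure, most of the concern falls away.

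**What to change.** **Needed, at low cost**
- Put a short pre-specified set of T0 prognostic covariates into the primary mixed model, instead of relying on a supplementary model with covariates chosen by observed imbalance. Age, sex, FAS and comorbidities are candidates that the trial already collects. The cost is a few degrees of freedom and a wording change in the protocol and SAP.
- Record and report by arm the numbers of patients eligible, approached and consented. The cost is a simple log in each practice.
- Name differential patient recruitment by arm as a limitation, separately from the skew among practices.

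**Where feasible, for practices not yet randomised**
- Before allocation is disclosed, have the practice list its currently known post-viral patients, for example those coded U09.9 or G93.3. The broad acute-infection codes (J06.9, J10/J11, U07.1) are unsuitable, because they would list many people without post-viral symptoms.
- Hold GP training until listed patients have been approached.
- Pre-specify a sensitivity analysis restricted to listed patients.

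This second part adds work for practices that the Discussion already describes as short of staff. The list will not cover patients who present later or have not raised their symptoms. Covariate adjustment cannot remove unmeasured differences such as motivation, so the limitation statement is needed in any case.
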